### Who will take informed consent? {26a}

Participants will be approached about the trial during their initial admission for T1D once acute treatment has restored metabolic stability. The treating doctor will provide information about the trial. The research team will also provide written information in the form of a Participant Information and Consent Form (PICF). The participant will be encouraged to ask questions and take time to consider the information. Consent will be sought by the study team. Minors (<18 years) will be fully informed about the research and given the opportunity to ask questions and to discuss the research with family, friends and a family doctor. A parent or guardian will provide formal consent.

### Additional consent provisions for collection and use of participant data and biological specimens {26b}

Blood samples collected throughout the study will be processed, frozen and stored for analysis to achieve the primary, secondary and exploratory objectives. If the participant consents, some of the sample may be stored indefinitely for other future research studies at the central study repository. Before any blood samples can be used for other research studies, approval from the hospital’s Human Research Ethics Committee will be obtained. If participants do not give consent for their blood samples to be used for future research, the samples will be discarded after analysis of the study endpoints is complete.

### Interventions

#### Explanation for the choice of comparators {6b}

Participants will receive either 4 mg/day orally of baricitinib or placebo for a duration of 48 weeks. Both groups will receive intensive diabetes management aimed at achieving near-normal metabolic control. Participants from both groups will continue to manage their blood glucose using insulin as per standard-of-care. As such, placebo has been chosen as the comparator for baricitinib.

#### Intervention description {11a}

Participants will be instructed to take one tablet from a bottle at about the same time each day (one tablet of baricitinib (4mg/tablet) or one tablet of placebo), with or without food, for 48 weeks. Baricitinib and placebo will be identical tablets manufactured by Eli Lilly.

#### Criteria for discontinuing or modifying allocated interventions {11b}

Treatment will be discontinued at the end of the treatment period or in certain cases if there is development of an adverse event reaction to the investigational product. In this clinical trial, an adverse event (AE) is any occurrence or worsening of an undesirable or unintended sign, symptom or disease whether or not associated with the treatment. In most cases, the investigational product will be transiently discontinued until the problem is resolved and participants will remain in the study. If the adverse event is severe, it may prevent continuation of the participant in the study. Serious adverse events (SAEs) are untoward medical occurrences that result in any of the following outcomes: death; a life-threatening adverse event; inpatient hospitalization or prolongation of existing hospitalization, with the exception of hospitalization relating to initial diagnosis of T1D; incapacity to conduct normal life functions; and congenital anomaly/birth defects in the offspring of a study participant. SAEs that will lead to permanent discontinuation from trial intervention for an individual participant include GI perforation, baricitinib hypersensitivity and venous thromboembolism.

Participants may also discontinue trial treatment if the participant or legal guardian requests to discontinue trial intervention, or the investigator decides to discontinue a participant from the trial intervention in case the participant:Is pregnantDemonstrates significant non-compliance with the trial interventionExperiences a serious or intolerable adverse event such that continued trial intervention would not be in the best interest of the participantDevelops, during the course of the trial, symptoms or conditions listed in the exclusion criteriaRequires a medication that is prohibited by the protocolRequires early discontinuation for any other reason

In addition, the progress of the study will be monitored by the Trial Management Group (TMG), which will review safety recommendations from the Safety Review Committee (SRC) and make decisions regarding continuation, termination or modification of the study. The SRC will perform regular reviews based on enrolment numbers of safety data and review of all SAEs and will make recommendations to the TMG for continuing, modifying or stopping the trial.

Events for review by the SRC in this trial include:Any death except those assessed as not related to study treatment on review by the protocol chairs, the clinical trial physician and the coordinating principal investigatorTwo or more of the first 10 treated participants or ≥20% of all treated participants experience a clinically significant, drug-related adverse event resulting in the permanent discontinuation of study treatmentAny gastrointestinal perforationVenous thromboembolismEvidence of serious opportunistic infection, including tuberculosis, or EBV-associated lymphoproliferative disorderAny unexpected, treatment-related SAE resulting in permanent treatment discontinuation and not related to glycaemic events

If the trial is terminated, the investigator may withdraw all trial participants from the trial treatment.

#### Strategies to improve adherence to interventions {11c}

The investigator will maintain adequate records of the disposition of the investigational product, including the date and quantity of drug that was received, the participants to whom drug was dispensed and an account of any destroyed drug. A drug-dispensing log will be kept current for each participant and will contain the identification of each participant and the date and quantity of drug dispensed and returned. Tablet counts will be used to assess participant compliance with daily doses of the study medication.

#### Relevant concomitant care permitted or prohibited during the trial {11d}

Combinations with other JAK inhibitors have not been studied and are not permitted. Participants who start a concomitant medication will be advised to contact the study team to review its potential effects on baricitinib metabolism. Those who require an emergency therapy will be encouraged to pursue the necessary clinical care and contact the study team within 24 h. Whenever possible, the recommendation will be to use concomitant medications that do not alter baricitinib levels.

#### Provisions for post-trial care {30}

Participants will be followed for 48 weeks after completion of the treatment period, including monitoring for any adverse events. Participants will be cared for by their local health care provider during and after completion of the study.

### Outcomes {12}

The primary endpoint of the study is plasma C-peptide area under the curve (AUC) over 2 h following a mixed meal tolerance test (MMTT) at 48 weeks.

The secondary endpoints of the study are:Change from baseline in 2-h MMTT-stimulated C-peptide AUC at weeks 12, 24, 72 and 96Change from baseline in mean daily insulin use over 7 consecutive days during the 2 weeks prior to the assessment at weeks 12, 24, 48, 72 and 96Change from baseline in glycosylated haemoglobin (HbA1c) levels at weeks 12, 24, 48, 72 and 96Number of participants with responder status at weeks 12, 24, 48, 72 and 96Change in estimated C-peptide (CP_EST_) [29] from baseline at weeks 12, 24, 48, 72 and 96Continuous glucose monitoring (CGM) at baseline, 12, 24, 48 and 96 weeksFrequency and severity of all adverse events.

The following mechanistic endpoints will be assessed at baseline, 12, 24, 48 and 96 weeksAnalysis of total and antigen-specific T cells, including tetramer analysisTreg analysis

The following mechanistic endpoints will be assessed at baseline, 24 and 96 weeksAssessment of IFNγ, IL-21 and IL-7 induced STAT1, STAT3 and STAT5 phosphorylation respectively in whole bloodPBMC analysis using flow cytometry, including markers for lineage, activation, exhaustion and cytokine signalling10x Chromium single cell sequencing

### Participant timeline {13}

**Table Tabb:** 

	Screening		48 weeks on study drug											48 weeks of follow-up	
Study visit	**1**	**2**	**3**	**4**	**5**	**6**	**7**	**8**	**9**	**10**	**11**	**12**		**13**	**14**
Time required (h)	**1**	**3**	**1**	**1**	**1**	**1**	**3**	**1**	**1**	**1**	**1**	**3**		**3**	**3**
*Study week*	*−4 to −1*		*0*	*2*	*4*	*8*	*12*	*16*	*20*	*24*	*36*	*48*		*72*	*96*
*Study day*			*0*	*14*	*28*	*56*	*84*	*112*	*140*	*168*	*252*	*336*		*504*	*672*
*Visit window, days*				±3	±3	±7	±7	±7	±7	±7	±7	±7		±14	±14
Clinical history	X														
Full examination	X														
Short examination, weight		X	X	X	X	X	X	X	X	X	X	X		X	X
Safety review and adverse events reporting			X	X	X	X	X	X	X	X	X	X		X	X
Study drug provided			X		X	X	X	X	X	X	X				
Pregnancy testing (if applicable)	X		X	X	X	X	X	X	X	X	X	X		X	X
Review of insulin use and diabetes control			X	X	X	X	X	X	X	X	X	X		X	X
Continuous glucose monitoring		X					X			X		X		X	X
Telephone contact			Regularly throughout the entire study												
Blood sampling	X	X	X	X		X	X	X	X	X	X	X	X	X	X
Mixed meal tolerance test		X						X			X		X	X	X

### Modifications to visit logistics and schedule in response to COVID-19

In response to the COVID-19 pandemic, the BANDIT trial is following the current advice of the Australian Department of Health as well as hospital specific restrictions at each study site to best mitigate the risk of SARS-CoV-2 infections amongst the participants and trial staff.

Adjustments have been made to study visits in order to reduce social contact where possible. These include allowing for visits to be conducted remotely via telehealth instead of face-to-face, local as opposed to tertiary site pathology collection, and delivery of the study drug by courier. On-site attendance has been limited to essential in-person visits, including the initial screening and consent visits, and visits that involve trial endpoints that are not routinely available at local pathology centres, such as the Mixed Meal Tolerance Test. Flexibility with the time windows of these visits has been increased to make them more achievable. Standard COVID-19 screening by questions as advised by local authorities is being conducted prior to each face-to-face visit and the visit re-scheduled if necessary.

In addition, all participants are encouraged to receive the full course of an Australian Government approved COVID-19 vaccination if eligible.

### Sample size {14}

The sample size of 83 participants was selected based on estimates of 2-h AUC mean C-peptide obtained from prior studies and using standard power calculations for comparison of treated and placebo groups [30, 31].

Using standard equations for comparison of two means, a sample size of 50 baricitinib treated and 25 placebo treated participants with complete data is needed to provide 80% power to detect 45% increase in mean log(C-peptide+1) (0.306 vs. 0.445, sd of 0.2), in the treated group using a two-sample *T*-test at 0.05 level of significance (two-sided). With the expected 10% dropout rate, the number of participants recruited into the study will be increased to 83 (55 and 28 in the intervention and control arms respectively). Should the number of drop-outs exceed 10%, additional participants may be recruited.

### Recruitment {15}

Recruitment will primarily occur through diabetes clinics and diabetologist’s private practices. In addition, a significant emphasis will be placed upon using social media platforms as a means of online advertisements. Furthermore, the study will be publicized in press releases, on-line through JDRF, via targeted emails and letters through Diabetes Australia and through the National Diabetes Services Scheme (NDSS) that distributes diabetes treatment consumables through pharmacies. Additional publicity or advertising may be conducted, with appropriate ethics approvals.

### Assignment of interventions: allocation

#### Sequence generation {16a}

Stratified block randomization with variable block sizes of 3, 6 or 9 will be used to generate the randomization schedule. This will be done by an independent researcher prior to study initiation. Age (<21 and ≥21 years) will be used as a stratification factor.

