#### Implementation {16c}

Randomization lists are generated by the trial statistician. Lists will then be provided to each site. Study coordinators or investigators responsible for enrolling participants will assign each participant to the next available randomization number from the appropriate age list.

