## Statistical methods

### Statistical methods for primary and secondary outcomes {20a}

All analyses will be performed using either SPSS 22 (IBM Corp. Armonk, NY, USA) or Stata15 (StataCorp LP, College Station, TX, USA). An experienced biostatistician will oversee data collection and data analysis. Primary analysis will be performed based on intention to treat (ITT) with sensitivity analysis as per protocol to confirm the robustness of the findings. In case of participants missing the follow-up assessment, appropriate imputation techniques will be employed in consultation with the study statistician. All continuous data will be tested for normality prior to the data analysis and appropriate transformations will be applied for skewed data. The C-peptide levels will be log transformed using log(C-peptide+1) as appropriate. ANOVA analysis will be used to examine the change in primary outcome between groups.

The baseline differences between study arms will be examined using *T*-test for continuous normally distributed data, while the Wilcoxon rank-sum test will be used for skewed or ordinal data and either chi-2 or Fisher’s exact for categorical data. Multilevel mixed effect model will be constructed to examine the impact of intervention on longitudinal changes in primary outcome while controlling for potential confounders including gender, baseline age and C-peptide level.

Secondary and exploratory outcomes will be assessed using either ANOVA or Fisher’s exact test for continuous and categorical data respectively. Multilevel mixed effect regression analysis will be used to examine longitudinal changes while controlling for potential confounders, either identified during the analysis or those of clinical relevance. The per-protocol analysis will be performed, including only those who received at least 50% of the treatment in order to confirm the robustness of the ITT results. Logistic regression will be used to examine the risk of developing adverse events (AE) or SAEs. Any deviations from the original data analysis plan will be documented and reported as appropriate.

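### Randomisation is stratified by age, but the named between-group tests carry no age term; if age is prognostic they are conservative and available precision is forgone

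*Protocol article*

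**What the plan says.** Sequence generation {16a} in the protocol article sets out blocked randomisation with one named stratification factor: "Age (<21 and ≥21 years) will be used as a stratification factor".

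Statistical methods for primary and secondary outcomes {20a} names the between-group comparison for the primary outcome: "ANOVA analysis will be used to examine the change in primary outcome between groups". No factor or covariate is attached to it. For the other outcomes, "Secondary and exploratory outcomes will be assessed using either ANOVA" or, for categorical data, Fisher's exact test, again with no stratum.

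The same section also plans a multilevel mixed model for longitudinal change in the primary outcome, adjusted for gender, baseline age and C-peptide. Mixed models are planned for secondary outcomes too, but their covariates are left open and age is not among any named. Nothing ranks the ANOVA above or below the mixed model. Outcomes {12} places the primary endpoint at a single time, week 48.

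Sample size {14} rests on a two-sample t-test with no covariates.

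**The concern.** Stratified blocks hold the age split nearly equal between arms, so variation due to the age stratum largely drops out of the treatment difference. An ANOVA with treatment as its only factor still counts that variation as residual error. Its estimated standard error then exceeds the true sampling error of the difference. Intervals are wider than they need be, and the test rejects less often than its nominal 5% under the null.

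At stake is precision. Only 25 placebo participants are expected to have complete data, so the precision that stratification provides is worth keeping. Choosing age to stratify on, and listing baseline age among possible confounders in the mixed model, suggests the investigators think age may matter for outcome.

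**Working it through.** **Inputs from Sample size {14}.** Means and SD on the log(C-peptide+1) scale: "0.306 vs. 0.445, sd of 0.2", a difference of 0.445 − 0.306 = 0.139. Numbers: "a sample size of 50 baricitinib treated and 25 placebo treated participants with complete data". Two-sided 5% level, 80% power. Allocation is 2:1 (Trial design {8}), in blocks of 3, 6 or 9 (Sequence generation {16a}).

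**Assumed inputs, not in the article.** R², the share of within-arm outcome variance explained by the age stratum, is taken as 0, 5, 10 and 20%, with the total SD held at 0.2. The share of participants under 21 is taken as 60%, with 75% as a check.

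**Step 1: reproduce the stated sample size.**
- Placebo n = (1.96 + 0.842)² × 0.2² × (1 + 1/2) / 0.139² = 24.4, so 25, with 50 on baricitinib.
- Standard error = 0.2 × √(1/50 + 1/25) = 0.0490; 0.139 / 0.0490 = 2.84.
- Power is 0.810 by the normal approximation and 0.7995 by the noncentral t.

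The plan's figure reproduces, for an unadjusted comparison.

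**Step 2: closed-form effect of leaving the stratum out.** With age balanced by design, the true standard error is √(1 − R²) times the one the unadjusted ANOVA reports.
- Excess interval width = 1/√(1 − R²) − 1: 0, 2.6, 5.4 and 11.8%.
- Type I error = 2 × [1 − Φ(1.96/√(1 − R²))]: 5.0, 4.4, 3.9 and 2.8%.
- For R² of 5, 10 and 20%, unadjusted power is about 0.807, 0.813 and 0.827. With the stratum in the model (SD = 0.2 × √(1 − R²), 72 df) it is 0.819, 0.839 and 0.879.

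**Step 3: simulation check.** Stratified permuted blocks of 3, 6 or 9 at 2:1, N = 75, 60% under 21, 10,000 runs per scenario, comparing ANOVA without and with the stratum:

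| Assumed R² | Type I error, without | Type I error, with | Excess width, without | Power, without | Power, with | Points forgone |
|---|---|---|---|---|---|---|
| 0% | 0.049 | 0.049 | 0% | 0.795 | 0.796 | 0.1 |
| 5% | 0.043 | 0.050 | 2.6% | 0.798 | 0.812 | 1.4 |
| 10% | 0.037 | 0.048 | 5.5% | 0.806 | 0.835 | 2.9 |
| 20% | 0.028 | 0.051 | 12% | 0.832 | 0.884 | 5.2 |

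Monte Carlo error is about √(0.8 × 0.2 / 10,000) = 0.004 for power and √(0.05 × 0.95 / 10,000) = 0.002 for type I error. The simulation and the closed form therefore agree closely. With 75% under 21 the results are similar: at R² = 20%, type I error 0.030, excess width 12%, power 0.817 without and 0.874 with the stratum.

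These figures concern a continuous outcome. Nothing was calculated for Fisher's exact test or responder status.

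**The case against.** The article says ANOVA, not one-way ANOVA. A condensed article may leave the factor list to the full protocol or the analysis plan, neither of which is shown. This has some force, and those documents may already include the stratum. But the same section lists covariates for the mixed model of the primary outcome and none for the ANOVA, and the sample size assumes an unadjusted test. As written, the tests do not follow the randomisation.

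Stronger readings are tempting, and the article does not support them:

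- *Age is ignored, because the mixed model is only supplementary.* The article does not call it that. It plans an age-adjusted model of the primary outcome and does not say which analysis is confirmatory.
- *The trial loses power against its plan.* The sample size assumed an unadjusted t-test with a total SD of 0.2. Unadjusted power stays between 0.795 and 0.832 over the range shown, so what is forgone is a possible gain above the planned 80%.
- *The harm is certain.* It is nil if the age stratum does not predict outcome, and the article gives no figure for that.
- *The test is invalid.* The error is conservative and false positives are not inflated.
- *Site is an undeclared stratum.* "Lists will then be provided to each site" might suggest this, but age is the only factor named, and how the lists are built is a detail the full protocol may settle.

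It is also fair to say that replacing Fisher's test is partly a matter of preference in a trial this small.

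**Conclusion.** The point holds in limited form. The named between-group tests omit the factor used to stratify randomisation, and it is left open whether the ANOVA or the age-adjusted mixed model is confirmatory. The cost is conditional and modest: negligible if age is not prognostic, rising at an assumed R² of 20% to intervals about 12% too wide, a type I error near 2.8% and about 5 points of power unused. The figures rest on the assumed R², 75 participants with complete data, a total SD of 0.2 and an additive age effect. This is a nearly free improvement in efficiency, not a correction of an invalid analysis.

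**What to change.** Include the randomisation stratum (<21/≥21, as randomised) as a fixed factor in the week-48 between-group model for the primary outcome and in each ANOVA-type secondary analysis. For responder status, use a test stratified by age where the counts allow, such as Cochran-Mantel-Haenszel or an exact stratified test. State whether the week-48 between-group model or the longitudinal mixed model is confirmatory.

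The cost is one degree of freedom per model and a few lines of wording, with no added participants, visits or procedures. If age proves not to be prognostic, almost nothing is lost: simulated power at R² = 0 is 0.796 with the stratum and 0.795 without. The change should be made before unblinding, so that no choice between adjusted and unadjusted results remains afterwards. If the full protocol or analysis plan already includes the stratum, a sentence saying so is enough.

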#### Concealment mechanism {16b}

A blinded list will be provided for the study coordinators and investigators to assign participants. This will be a list of numbers, with no information on what treatment is assigned. The study coordinator or investigator will assign the next available randomization number from the age appropriate list and will complete a prescription form specifying the randomization number.

The randomization lists sent to the pharmacy at each site will contain the treatment assignments for each randomization number. The pharmacy will dispense the correct treatment for that number according to their randomization list.

#### Implementation {16c}

Randomization lists are generated by the trial statistician. Lists will then be provided to each site. Study coordinators or investigators responsible for enrolling participants will assign each participant to the next available randomization number from the appropriate age list.

### Assignment of interventions: blinding

#### Who will be blinded {17a}

Study participants, coordinators, investigators, study staff, sponsor and sponsor’s representatives will be blinded to assignment of participants.

#### Procedure for unblinding if needed {17b}

Unblinding prior to study completion will occur if a participant’s well-being is threatened and the investigator believes unblinding is necessary to provide appropriate medical care or to protect the participant.

Unblinding envelopes will be provided to each site. These envelopes will be stored securely by the Study Coordinator/ Principal Investigator in the study files. One envelope will be provided for each randomization number, and will contain the treatment assignment information (active drug or placebo) for that number, in case emergency unblinding is necessary.

